## Abstract

Stimulation of the vagus nerve, a parasympathetic nerve that controls the neuro-digestive, vascular, and immune systems, induces pain relief, particularly in clinical conditions such as headache and rheumatoid arthritis. Transmission through vagal afferents towards the nucleus of the solitary tract (NST), the central relay nucleus of the vagus nerve, has been proposed as the main physiological mechanism that reduces pain intensity after vagal stimulation. Chronic pain symptoms of fibromyalgia patients might benefit from stimulation of the vagus nerve via normalization of altered autonomic and immune systems causing their respective symptoms. However, multi-session non-invasive vagal stimulation effects on fibromyalgia have not been evaluated in randomized clinical trials. We propose a parallel group, sham-controlled, randomized study to modulate the sympathetic–vagal balance and pain intensity in fibromyalgia patients by application of non-invasive transcutaneous vagus nerve stimulation (tVNS) over the vagal auricular and cervical branches. We will recruit 136 fibromyalgia patients with chronic moderate to high pain intensity. The primary outcome measure will be pain intensity, and secondary measures will be fatigue, health-related quality of life, sleep disorders, and depression. Heart rate variability and pro-inflammatory cytokine levels will be obtained as secondary physiological measures. We hypothesize that multiple tVNS sessions (five per week, for 4 weeks) will reduce pain intensity and improve quality of life as a result of normalization of the vagal control of nociception and immune–autonomic functions. Since both vagal branches project to the NST, we do not predict significantly different results between the two stimulation protocols.

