Since fibromyalgia involves a dysregulation of the autonomic (high sympathetic tone) and immune (enhanced pro-inflammatory activity) systems [25,41], non-invasive tVNS is expected to improve the symptoms of fibromyalgia, including chronic, musculoskeletal, and generalized pain [42,43], through modulation of the vegetative and immune systems [44]. The main objective of this intervention study is to evaluate the effects of repeated sessions of tVNS on pain and other symptoms in fibromyalgia patients, comparing auricular and cervical tVNS protocols which have been probed in other pathologies [45,46,47,48,49]. According to the effectivity reported in these studies, we hypothesize that a multi-session auricular and cervical tVNS protocol carried out under safety standards will provide analgesic and therapeutic effects in fibromyalgia patients, in comparison with sham and axillary nerve stimulation controls, and secondarily will also normalize the autonomic (via heart rate variability) and immune (via pro-inflammatory cytokine levels) functions supposedly altered in this disease.

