Sample size calculation will be based on the hypothesized significant differences between (auricular vs. cervical vs. sham vs. axillary) and within (baseline vs. post-intervention) groups. We conducted an a priori calculation of the sample size by the GPower statistical power analysis tool (3.1.9.2) for a mixed-model repeated-measures ANOVA (with groups and pre/post-intervention measures as levels of the between-group and within-group factors) [50], as a primary outcome parameter conducted for the pain questionnaire (BPI). Because the main parameter of interest for this calculation is the interaction between the factors group and measure, we conducted the analysis for the within–between interaction, setting the following input parameters: effect size (f) = 0.2 (medium size), α value = 0.05, Power (1-ß) = 0.95, number of groups = 4 (pooled sham, axillary stimulation, cervical tVNS, and auricular tVNS), number of measurements = 2 (baseline as pre-intervention, and at the end of the intervention), correlation for repeated measures = 0.5, and with nonsphericity correction (1). The output parameters were: non-centrality parameter = 17.92, critical F = 2.68, actual power 0.951, and total sample size = 112. Taking into account these estimates and adding 20% to the calculated sample to compensate for possible dropouts, we will include 34 patients per group (total sample size of 136).

Written informed consent (available in Supplemental material) will be provided by all patients prior to their participation in the study. The clinical trial will be submitted for consideration and approval by the Regional Ethics Committee for Clinical Studies. In accordance with national legislation (93/42/EEC and RD 1090/2015), the study will be pre-registered in the Spanish registry of clinical studies (https://reec.aemps.es/reec/public/web.html#, accessed on 28 December 2021). The study complies with the code of Ethics of the World Medical Association Declaration of Helsinki (amend 64th, 2013).

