### 2.6. Statistical Analysis

To exclude differences of baseline measurements (BPI scores as primary outcome measure, and FIQR, PGIC, PSQI, and BDI scores as secondary outcome measures) between groups, a mixed model 4 × 4 ANOVA will be used, with one between-group factor with four levels (4 groups), and one within-subject factor (four baseline measurements). A mixed model 4 × 8 ANOVA, with one between-group factor with four levels (four groups) and one within-subject factor (8 measurement days), will be used to analyze the scores of the outcome measures obtained in each of the questionnaires throughout the study (intra-intervention and follow-up period). In case of significant results of the ANOVAs, exploratory Bonferroni-corrected post-hoc *t*-tests will be conducted. A univariate analysis by a Chi-square test will be performed to explore the success of blinding with regard to the intervention, and *t*-tests as well as Chi-square tests will be conducted to exclude demographic differences (gender, age, and years of education) between groups. Pearson’s correlation coefficient (Pearson’s *r*) will be calculated for each tVNS group to analyze possible correlations between vagal activity measures (heart rate variability) during the intervention and questionnaire scores (FIQR, BPI, PGIC, PSQI, and BDI), as well as between pre- and post-intervention pro-inflammatory cytokines levels and outcome measures. The critical level of significance for all statistical analyses will be set to *p* < 0.05. The analyses will be carried out using the SPSS statistical software package.

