## 3. Discussion

This study aims to explore the effects of multiple tVNS sessions on fibromyalgia symptoms. Because the vagus nerve modulates afferent pain signals to the central nervous system and the tone of the autonomic, immune, and emotional systems [19], the application of tVNS, a non-invasive low-intensity electric stimulation technique with potential to activate A- and B-fibers [75], might normalize the functions of vagal afferences, which seem to be pathologically altered in fibromyalgia [25], and thus reduce the characteristic symptoms of this disease, particularly muscular and generalized pain. Encouraging results have been reported for invasive vagal stimulation procedures in fibromyalgia treatment [31], but controlled clinical trials using non-invasive vagal stimulation are missing with respect to the effectiveness and safety of this neuromodulation option. The proposed study might shed light on the involvement of vagal activity and sympathetic–vagal balance in chronic pain and other symptoms of patients with fibromyalgia and also provide direct comparisons between two tVNS protocols in terms of effectiveness and safety. In particular, we hypothesize that this protocol of vagal neuromodulation is effective and safe for improving pain and other symptoms in these patients. The inclusion of a sham intervention condition is important to demonstrate the specificity of the therapeutic effectivity of this intervention. The inclusion of an active control condition, in which a nerve not related to fibromyalgia symptoms (the axillary nerve) is stimulated, will deliver further evidence about the specificity of the effects. The high number of intervention sessions (20 sessions, over 4 weeks) included in this stimulation protocol might serve to control for null effects of tVNS due to under-dosing.

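### The auricular-cervical comparison is promised, but it is tested only behind a significant ANOVA and predicted as an absence of significance, so it may go unmade or leave moderate differences open

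*Protocol article*

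**What the plan says.** The Abstract gives the expectation for the two active protocols as "we do not predict significantly different results between the two stimulation protocols", on the ground that both vagal branches project to the same brainstem nucleus. It states no direction and no margin.

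The comparison is not incidental. The main-objective sentence of the Introduction includes "comparing auricular and cervical tVNS protocols which have been probed in other pathologies", and the Discussion says the study might "provide direct comparisons between two tVNS protocols in terms of effectiveness and safety".

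Section 2.6 plans a four-group mixed ANOVA over eight measurements. Pairwise comparisons appear only as "exploratory Bonferroni-corrected post-hoc" t-tests, conditional on a significant ANOVA. The number of pairs in the Bonferroni family is not given.

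In section 2.1 the power calculation uses "effect size (f) = 0.2 (medium size), α value = 0.05, Power (1-ß) = 0.95, number of groups = 4" and states that "we conducted the analysis for the within–between interaction". It takes "number of measurements = 2 (baseline as pre-intervention, and at the end of the intervention". The auricular-cervical contrast has no power calculation of its own.

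**The concern.** The expectation is phrased in terms of significance, so any non-significant auricular-cervical test agrees with it, whatever the reason for the non-significance. Low power and the Bonferroni correction both make that agreement easier to reach.

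The gate adds a second problem. If the ANOVA is not significant, the plan as written produces no auricular-cervical comparison at all, although the article lists it among its aims.

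The stake is the comparative question. The Conclusions say the findings will help to design later trials. An impression that the two protocols perform alike could carry over to the choice of protocol without the data supporting it. The comparison of active with control stimulation is not affected.

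**Working it through.** **1. Reproduce the plan's own figure.** Inputs from section 2.1: f = 0.2, α = 0.05, 4 groups, m = 2 measurements, correlation ρ = 0.5, N = 112.

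- Non-centrality: λ = f² × N × m / (1 − ρ) = 0.04 × 112 × 2 / 0.5 = 17.92, as stated.
- With 3 and 108 degrees of freedom, critical F = 2.689 (printed as 2.68) and power = 0.951, as stated.
- 112 / 4 = 28 per group. 112 × 1.2 = 134.4, rounded up to 136 = 4 × 34.

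The calculation is correct for the four-group interaction.

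**2. Scale for the contrast.** The SD of the change score is SD × √(2(1 − ρ)) = SD × √(2 × 0.5) = SD. Change-score and raw SD therefore coincide under the plan's inputs.

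**3. Precision of auricular minus cervical.** SE = √(2/n) in SD units, and the 95% half-width is t × SE.

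- n = 34: SE 0.2425, t 1.997, half-width 0.484 SD.
- n = 34 × 0.8 = 27.2 (20% loss): SE 0.2712, t 2.006, half-width 0.544 SD.

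If the observed difference is zero, the interval reaches about 0.5 SD either way. If the result is just non-significant without correction, it reaches twice the half-width: 0.97 SD (n = 34) or 1.09 SD (n = 27.2).

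**4. Chance of a non-significant test** (noncentral t, two-sided). The corrected columns assume that Bonferroni covers all six pairs of four groups (α/6).

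| True difference | n = 34, uncorrected | n = 27.2, uncorrected | n = 34, α/6 | n = 27.2, α/6 |
|---|---|---|---|---|
| 0.4 SD | 0.631 | 0.695 | 0.849 | 0.887 |
| 0.5 SD | 0.471 | 0.559 | 0.736 | 0.804 |
| 0.8 SD | 0.098 | 0.175 | 0.283 | 0.415 |

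For scale: if the two active groups are equal and the two control groups are equal (an assumption), λ/N = 17.92/112 = 0.16, so f on the change score is 0.4. That is ±0.4 SD around the mean, an active-control difference of 0.8 SD.

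**5. Sensitivity to the contrast chosen.** Averaging eight post-baseline visits at a between-visit correlation of 0.5 (an assumption) multiplies the SD by √((1 + 7 × 0.5)/8) = 0.75.

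- The half-width falls to 0.484 × 0.75 = 0.36 SD (n = 34) or 0.544 × 0.75 = 0.41 SD (n = 27.2).
- With the SE multiplied by 0.75, the chance of non-significance at a constant 0.5 SD falls to 0.227 (n = 34) or 0.325 (n = 27.2) uncorrected, and to 0.485 or 0.603 at α/6.

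A baseline-adjusted single-visit analysis at ρ = 0.5 multiplies the SD by √0.75. At n = 34 the half-width is then about 0.42 SD.

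**The case against.** The strongest reply is that the article never commits to reading non-significance as similarity. Its formal hypotheses concern benefit and safety of tVNS, with sham and axillary stimulation as comparators. The quoted sentence can be read as declining to predict a difference. The pairwise tests are labelled exploratory, and the study calls itself a pilot. This stands: a reader might infer that p > 0.05 will be declared equivalence, but no such decision rule is stated.

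A reader might also infer that the design cannot exclude a large difference. The figures do not support that. If the true difference is zero, a 90% CI would exclude 0.8 SD in about 81% of trials (28 per arm) to 90% (34 per arm), and a 95% CI in about 67% to 80%. At a true difference of 0.8 SD the uncorrected test usually detects it. The weakness concerns moderate differences.

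The percentages also depend on choices the article leaves open, namely the Bonferroni family and the visit or average to be contrasted. An average over visits would be more precise, as shown above; a single-visit post-hoc test would not gain that.

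Finally, naming a contrast and its time point is often left to a SAP, which is not shown. That answers a complaint of missing detail. It does not answer the gate or the significance-based prediction, both of which the article itself fixes.

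**Conclusion.** The point holds as a mismatch between a stated comparative aim and the stated way of addressing it. Under section 2.6 the auricular-cervical comparison is made only after a significant ANOVA. A non-significant result then fits the Abstract's prediction automatically.

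Such a result would be weak evidence. On the pre/post change score it leaves open from about 0.5 to about 1 SD, and a true 0.5 SD difference would be missed about half the time uncorrected and about three-quarters of the time or more with a six-pair correction. These figures rest on the plan's correlation of 0.5, on 34 per arm or 27.2 after 20% loss, and, for the corrected ones, on the six-pair assumption. Averaging visits would lessen the problem without removing it.

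This is a risk created by the wording and the gate. It is not a stated rule that equates non-significance with equivalence, and it does not show that large differences are beyond the trial's reach.

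**What to change.** In section 2.6, prespecify the auricular-minus-cervical difference in BPI at the end of the intervention as an estimate with its 95% CI, reported whatever the omnibus ANOVA shows. State that p > 0.05 will not be read as similarity. Reword the prediction in the Abstract to match, for example as an expectation about the size of the difference that the trial will estimate.

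A claim of similarity would need a margin fixed in advance by the sponsor, and the documents give none. For orientation, two one-sided tests at α = 0.05 with 80% power and a true difference of zero need n = 2 × ((1.645 + 1.282)/margin)² per arm. That is 69 for a margin of 0.5 SD, 108 for 0.4 SD and 191 for 0.3 SD, against 34 planned. These margins only illustrate the range.

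Without a similarity claim, the change needs no extra patients, visits or measurements. The cost is a more cautious conclusion about the two protocols.

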## 1. Introduction

Fibromyalgia is a disabling chronic disease. In addition to chronic and generalized pain, the syndrome includes extreme fatigue, insomnia and other sleep disorders, affective and emotional disorders, such as depression and anxiety, cognitive impairment, paresthesia, allergy symptoms, joint stiffness, tendinopathy, neuropathic and rheumatologic symptoms, chemical and skin hypersensitivity, irritable bowel syndrome, and other symptoms whose common etiopathogenesis is unknown [1,2,3]. Because of the unknown biological mechanisms of fibromyalgia, current pharmacological therapies are aimed at alleviating its symptoms, and the efficacy of available treatments is limited [4]. Moreover, generalized pain and extreme fatigue are usually refractory to any therapeutic attempt [4,5].

The parasympathetic vagus nerve (the 10th cranial nerve) innervates multiple internal organs and integrates sensory, motor, and autonomic information by four vagal nuclei. The primary central relay of vagal afferents is the nucleus of the solitary tract (NST) in the brainstem, and several branches of this nucleus project to different brain areas [6]. The myelinated A- and B-fibers of the vagal nerve send somatosensory, motor, and autonomic signals [7], and the complex system of vagal projections is involved in inflammatory, immune, nociceptive, and emotional processes [8,9]. A relevant role of the vagal nerve in pain processing is the transmission of peripheral inflammation signals to the central nervous system [10]. Additionally, neuroimaging studies have identified neuromodulatory activity in areas related to the sensory and emotional processing of pain, such as the insular cortex and anterior cingulate cortex, after vagal stimulation [11], which reveals that the central system of pain processing receives vagal afferences. Due to the multi-system control of the vagal nerve [12], some clinical conditions refractory to conventional treatment, such as epilepsy, depression, and inflammatory diseases, have been shown to benefit from invasive stimulation of this nerve [13]. Recent clinical and experimental studies have shown that stimulation of the vagus nerve also has therapeutic potential in other diseases, including pain syndromes [14,15]. Vagus nerve stimulation is a Food and Drug Administration (FDA)-approved somatic treatment for different pathologies. The precise mechanisms through which vagal stimulation induces clinical improvements are not well understood in detail [16,17], but regulation of the autonomic and immune systems and a specific effect on chemical mediators of inflammation are relevant physiological mechanisms of this intervention [18].

Considering that the vagus nerve controls pain signals towards the central nervous system [14,19,20], and growing evidence of autonomic dysfunction in fibromyalgia in terms of sympathetic hyperactivity [21,22,23,24,25,26,27], it can be argued that rebalancing the sympathetic–parasympathetic activity via vagal stimulation might reduce the intensity of pain and stabilize the autonomic symptoms of this disease. In addition, an immune system alteration [28] seems to mediate the interaction between the autonomic nervous system and the chronic inflammatory state in fibromyalgia, apparently by the influence of inflammatory cytokines and chemokines [28,29,30]. This well-described inflammatory state in fibromyalgia patients is critically important for treatment approaches. Auricular and cervical vagus nerve stimulation might reduce such inflammatory overactivity as well via efferent modulation of the activity of the spleen and inflammatory processes [18] and hereby reduce pain symptoms [19]. In accordance, invasive vagal nerve stimulation has been shown to be effective in treatment-resistant fibromyalgia patients, with a tolerability profile similar to that described for the treatment of epilepsy and depression [31]. However, to the best of our knowledge, the potential of non-invasive auricular and cervical vagus nerve stimulation under repeated sessions to improve fibromyalgia symptoms has not been evaluated in randomized, sham-controlled clinical studies. Auricular and cervical transcutaneous vagus nerve stimulation (tVNS), two non-invasive low-intensity electric stimulation procedures [32,33], have however been explored with respect to their potential to modulate the activity of this nerve in other clinical settings [20,34,35,36,37], and the effectiveness of these non-invasive methods might not differ significantly from those of invasive stimulation, while non-invasiveness provides an advantageous safety profile [14,19,38,39,40]. 

Since fibromyalgia involves a dysregulation of the autonomic (high sympathetic tone) and immune (enhanced pro-inflammatory activity) systems [25,41], non-invasive tVNS is expected to improve the symptoms of fibromyalgia, including chronic, musculoskeletal, and generalized pain [42,43], through modulation of the vegetative and immune systems [44]. The main objective of this intervention study is to evaluate the effects of repeated sessions of tVNS on pain and other symptoms in fibromyalgia patients, comparing auricular and cervical tVNS protocols which have been probed in other pathologies [45,46,47,48,49]. According to the effectivity reported in these studies, we hypothesize that a multi-session auricular and cervical tVNS protocol carried out under safety standards will provide analgesic and therapeutic effects in fibromyalgia patients, in comparison with sham and axillary nerve stimulation controls, and secondarily will also normalize the autonomic (via heart rate variability) and immune (via pro-inflammatory cytokine levels) functions supposedly altered in this disease.

## 2. Materials and Methods

### 2.1. Participants

Adult fibromyalgia patients, in an age range between 18 and 69 years, recruited from the Hospital Juan Ramón Jiménez of Huelva, Spain, will be interviewed to voluntarily participate in this monocentric study. Inclusion criteria will be the diagnosis of fibromyalgia by a physician, based on the 2010 American College Rheumatology (ACR) fibromyalgia diagnostic criteria, and the maintenance of characteristic symptoms for more than a year. A moderate to high pain intensity according to analog pain scales (above 4 points over 10), maintained for more than 6 months, will also serve as an inclusion criterion. The usual individual medical treatment for fibromyalgia will be maintained throughout the study, including psychopharmacological treatments. All genders will be included. Exclusion criteria will include standard conditions to be considered for VNS (cardiac arrhythmia, sleep apnea, pregnancy, etc.) [49], other chronic diseases producing widespread pain not related to known symptoms of fibromyalgia, multiple pharmacological treatments for symptoms different from those of fibromyalgia, primary psychiatric syndromes (psychosis, bipolar disorder, etc.) with or without treatment via central nervous system-acting medication, drug dependence (including smoking), vagal syndrome or history of vagal symptoms, and chronic pain and fibromyalgia secondary to inflammatory rheumatic diseases. Previous interventions with non-invasive brain stimulation methods or invasive VNS will also constitute exclusion criteria. An electrocardiogram will be performed in all participants before the study. Participants with arrhythmia and other cardiac alterations will be excluded from the study.

Sample size calculation will be based on the hypothesized significant differences between (auricular vs. cervical vs. sham vs. axillary) and within (baseline vs. post-intervention) groups. We conducted an a priori calculation of the sample size by the GPower statistical power analysis tool (3.1.9.2) for a mixed-model repeated-measures ANOVA (with groups and pre/post-intervention measures as levels of the between-group and within-group factors) [50], as a primary outcome parameter conducted for the pain questionnaire (BPI). Because the main parameter of interest for this calculation is the interaction between the factors group and measure, we conducted the analysis for the within–between interaction, setting the following input parameters: effect size (f) = 0.2 (medium size), α value = 0.05, Power (1-ß) = 0.95, number of groups = 4 (pooled sham, axillary stimulation, cervical tVNS, and auricular tVNS), number of measurements = 2 (baseline as pre-intervention, and at the end of the intervention), correlation for repeated measures = 0.5, and with nonsphericity correction (1). The output parameters were: non-centrality parameter = 17.92, critical F = 2.68, actual power 0.951, and total sample size = 112. Taking into account these estimates and adding 20% to the calculated sample to compensate for possible dropouts, we will include 34 patients per group (total sample size of 136).

Written informed consent (available in Supplemental material) will be provided by all patients prior to their participation in the study. The clinical trial will be submitted for consideration and approval by the Regional Ethics Committee for Clinical Studies. In accordance with national legislation (93/42/EEC and RD 1090/2015), the study will be pre-registered in the Spanish registry of clinical studies (https://reec.aemps.es/reec/public/web.html#, accessed on 28 December 2021). The study complies with the code of Ethics of the World Medical Association Declaration of Helsinki (amend 64th, 2013).

